### *2.2 STUDY DESIGN*

Bridge will be implemented in four cities, in Kazakhstan: Almaty, Shymkent, Temirtau & Karaganda. Due to their geographical proximity of Temirtau and Karaganda, and overlapping administration of HIV clinics they will be considered as one “site” for intervention roll out. In month 16, we will use computer software to sequentially randomly assign the three sites six months prior to implementing BRIDGE in months 22, 28 and 34.

We opted for a stepped wedge trial over a cluster RCT for ethical reasons so that all clusters will eventually receive the intervention as well as to avoid contamination and to be able to control for exogenous time specific effects as discussed earlier. The unit under experimental control will be a city, with the timing of roll-out of BRIDGE in each of the study’s cities—Almaty, Shymkent Karaganda, and Temirtau—to be randomly assigned. Since the cities are geographically disparate (with the exception of Karaganda and Temirtau, which is why we will consider them as a single study site) the likelihood of participant contamination is minimal.

The stepped wedge approach represents a scientific alternative to the randomized control trial (RCT) by providing a valid counterfactual to evaluate the impact of BRIDGE compared to the TP Standard of Care. This roll out design also more closely resembles the method of implementing BRIDGE in a real-world setting. The use of multiple groups and our data analytic plan will allow us to control for exogenous time-specific effects, such as introducing new HIV initiatives or funding cuts and minimizes contamination as all TP sites in a city will receive BRIDGE at the same time. More importantly, this design addresses important ethical considerations of communities by ensuring that all TP sites will eventually receive BRIDGE, which is a potentially lifesaving intervention.

The following figure describes the stepped-wedge rollout of Bridge in the four cities (with Karaganda & Temirtau combined as one study site):

Figure 2: Stepped Wedge Design

[figure not shown]

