Analysis of Program data: Formal hypothesis testing based on program data will test for differences in outcome measures obtained during the pre-intervention period (i.e., time points before BRIDGE is implemented in a city) versus periods when BRIDGE is implemented. We will employ permutation tests (a.k.a. “randomization tests”) for significance testing because of concerns that the distribution of measures may not be approximated well by a small sample size (i.e.,  $N=24$  TPs). In experimentally controlled trials with small sample sizes, permutation tests have been shown to be superior to parametric tests. As a heuristic and non-parametric approach, permutation testing more accurately estimates the nominal type I error rate for cluster randomized clinical trials with small sample sizes and with measures that may not be normally distributed compared to candidate parametric procedures. Strong hypothesis testing in this manner involves permuting the BRIDGE implementation status of each time point; since the time period “assignment” (pre-implementation vs. BRIDGE) is allocated based on city, permutations will account for clustering by city (i.e., a permutation for TPs in the same city will all be assigned the same implementation status for that time point). Not only does this conservatively account for shared variance that might be present due to being located in the same city, statistical efficiency can be improved by clustered permutation testing. For inference, the test statistic (difference in means) observed based on actual period assignments is compared vis-à-vis the distribution of test statistics using permuted assignments, with the proportion of permuted test statistics greater than the actual observed taken as the one-sided or half of the two-sided p-value. With program measures collected quarterly over 42 months, the number of clustered permutations with 3 study sites (4 cities) is 38,416, allowing testing of statistical significance with  $\alpha < .0001$ . If we permute all 24 TPs independently, tests of significance can be performed with much lower  $\alpha$ . We will conduct both permutation tests with sites permuted independently as well as clustered permutations by city and report the result with the more conservative p-value. Hypothesis testing for Aims 1 and 2—i.e., estimating the effectiveness of the intervention—will involve

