### 3.4. PROCEDURES FOR EACH COMPONENT OF BRIDGE STUDY

#### *BRIDGE Intervention Procedures*

As described above, BRIDGE will be rolled out in 6-month intervals between study sites (Karaganda and Temirtau will implement BRIDGE at the same time). Trust points will implement the BRIDGE intervention with guidance and support from the BRIDGE study team. The BRIDGE study team will provide initial training (described below) and follow-up trainings.

BRIDGE trust points will recruit PWID for testing through the SNS recruitment strategies, provide rapid testing for HIV in accordance with existing trust point protocols and link those with reactive tests (or known positives who have fallen out of care) to HIV care at the AIDS Centers. The intervention involves several handouts and supplementary materials as described in the BRIDGE Program Manual. In order to promote Trust Point ownership of the intervention, and to decrease any potential negative associations with CU or GHRCCA (which is affiliated with CU) we are requesting to distribute a number of supplementary materials without CU or GHRCCA logos or IRB approval stamps. These materials include recruitment materials that will be distributed throughout the community, specifically: trust point staff BRIDGE business cards, release of information form for ARTAS referrals, appointment cards for ARTAS referrals to other service providers, rapid testing informational brochure, ART informational brochure, and rapid testing coupons.

As an implementation science intervention, BRIDGE trust points will control participant consent procedures, monitoring, and retention of participants. All Trust Point staff who implement the BRIDGE intervention receive human subjects protection training from GHRCCA staff. Trust points are governed by a number of existing regulations regarding patient privacy, and all trust point services are provided anonymously in Kazakhstan. The BRIDGE intervention materials and handouts are designed to allow flexibility for trust points to adhere to their regulations: materials refer to both clients and peer recruiters by ID codes rather than names, and clients are permitted to take part in all components of the BRIDGE program anonymously, as they are permitted to receive all trust point services anonymously. The Republican AIDS Center and Almaty City AIDS Center have reviewed all

BRIDGE intervention materials to ensure that they do not violate these regulations.

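### The permutation count of 38,416 and the claimed resolution of alpha < .0001 do not fit a randomisation of three sites to three dates, which has only 6 possible outcomes and a smallest p of 0.167 one-sided

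*Combined protocol and SAP*

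**What the plan says.** **Randomisation (protocol 2.2, Study Design).** Software will "sequentially randomly assign the three sites six months prior to implementing BRIDGE in months 22, 28 and 34". Karaganda and Temirtau are close together, "which is why we will consider them as a single study site". The same section says "The unit under experimental control will be a city" and that "all TP sites in a city will receive BRIDGE at the same time". Section 3.4 confirms that "BRIDGE will be rolled out in 6-month intervals between study sites".

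**Test (protocol 2.4, Analysis of Program data).** Significance is to come from permutation tests, also called randomisation tests, on the difference in means between pre-implementation and BRIDGE periods. The implementation status of each time point is permuted, with all trust points (TPs) in a city moved together. For quarterly data over 42 months, "the number of clustered permutations with 3 study sites (4 cities) is 38,416", and this is said to allow alpha < .0001. The section adds: "If we permute all 24 TPs independently, tests of significance can be performed with much lower" alpha. Both versions are to be run, and the more conservative p-value reported. The p-value is defined "with the proportion of permuted test statistics greater than the actual observed taken as the one-sided or half of the two-sided p-value".

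**Related text.** The power paragraph in 2.4 uses two-tailed testing at alpha .05. The Data Analysis Plan for Primary Study Aim repeats the permutation test without the count, then says that hypothesis testing will rely on GLMM and GEE with sandwich variances.

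**The concern.** A randomisation test gets its validity from comparing the observed allocation with the other allocations that the randomisation could have produced. The plan claims a reference set of tens of thousands, yet the design in 2.2 allocates three units to three dates. If the claimed set is not the design's set, a very small p-value would look like evidence from the randomisation when it is not.

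This matters for the primary aim, because the permutation test is the method named for significance testing. A stepped wedge also confounds BRIDGE with calendar time: BRIDGE periods always come later. Section 2.2 says the analysis will control for time-specific effects, but an unadjusted difference in means does so only if the reference set preserves the time structure.

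**Working it through.** **Inputs**
- Randomised units: 3 sites (2.2).
- Switch dates: months 22, 28 and 34, one site each (2.2).
- Time points: 42 months / 3 = 14 quarters (2.4).
- Data collection starts in month 13 (Appendix A), so there are (22 − 13)/3 = 3, (28 − 13)/3 = 5 and (34 − 13)/3 = 7 pre-implementation quarters.
- Test level: two-sided .05 (2.4, power paragraph).

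**Step 1: reproduce the plan's figure.** 14^4 = 38,416 exactly. This gives each of four cities its own free choice of 14 switch quarters. The smallest p would be 1/38,416 = 0.000026 one-sided, or 0.000052 doubled, which is where alpha < .0001 comes from.

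**Step 2: the plan's logic with its own number of sites.** The sentence itself says three study sites. 14^3 = 2,744, so the smallest p is 1/2,744 = 0.00036 one-sided, or 0.00073 doubled. Alpha < .0001 is not reached.

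**Step 3: the design's reference set.** Three sites to three fixed dates, each used once, gives 3! = 6. The smallest p, counting the observed assignment, is 1/6 = 0.167 one-sided, or 2/6 = 0.333 by the plan's doubling rule. A noise-free step effect (0 before, 1 after) also gives p = 0.167. Power at two-sided .05 is therefore zero for any effect size.

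**Step 4: would treating the four cities separately help?** This contradicts 2.2, but as a sensitivity check:

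| Assumed randomisation | Assignments | Smallest p, one-sided | Smallest p, two-sided |
|---|---|---|---|
| 3 sites, 3 dates (as in 2.2) | 6 | 0.167 | 0.333 |
| 4 cities, 4 distinct dates | 24 | 0.042 | 0.083 |
| 4 cities, 3 dates, any two sharing | 36 | 0.028 | 0.056 |

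None reaches two-sided p < 0.05.

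**Step 5: behaviour of the test as written.** The text and the count describe different procedures. The text shuffles the status of each time point, while 14^4 permutes the start quarter of each city. Both were simulated with no true effect: 3 sites, 8 TPs each, 14 quarters, starts at quarters 4, 6 and 8, TP-quarter residual SD 1, site SD 0 or 0.5. The start-time version used the 14^3 set. The trend sizes are assumptions; the documents give none.

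| Linear trend common to all sites | Status shuffled: two-sided type I error at .05 | Start times permuted |
|---|---|---|
| None | about 5% | 0 to 2% |
| 0.02 SD per quarter | about 20% | 0 to about 2% |
| 0.05 SD per quarter | about 77% | under 1% to about 3% |

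In a separate start-time simulation with other noise assumptions, an abrupt common step at quarter 5 took the rate to at most about 6%. Permuting start times thus showed no large inflation here, but nothing in the randomisation guarantees its level.

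**The case against.** The strongest reply is that the plan does not restrict itself to the six assignments and has safeguards. Several stronger readings that a reader might infer fail for that reason.

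- **That the planned test cannot give p < 0.05.** As written, it can. The limit of 0.167 applies to a test confined to the actual randomisation. A larger reference set makes the p-value depend on an assumption; it does not make significance impossible.
- **That the planned test is bound to be inflated.** Only one of the two readings of the text gives the 20% and 77% rates. Both readings have support in 2.4, and the documents do not choose between them.
- **That counting only statistics greater than the observed one gives a 1 in 6 false-positive rate.** That rate would arise only if the rule were applied to the six-assignment set, which the plan never uses. In a set of 38,416, counting the observed assignment changes p by about 0.00003. The rule matters only once the reference set is corrected.
- **That permuting 24 TPs independently could lower the reported p.** The rule of reporting the more conservative result prevents this. It does not cure the main problem, because neither version uses the set of assignments the design could produce.
- **That no other analysis is planned.** GLMM and GEE are named for the same hypotheses. The documents do not say which result is primary.

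What remains is the wrong count, the wrong resolution and a reference set without a basis in the design.

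**Conclusion.** The point holds in this form. The arithmetic of 38,416 is reproducible, but it counts four independently timed cities with free switch dates, whereas the design randomises three sites to three fixed dates. Alpha < .0001 is unsupported even on the plan's own logic with three sites.

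The counts and minimum p-values follow directly from 2.2 and need no assumption beyond each order of the three sites being possible and equally likely. Any permutation p below 0.167 one-sided would come from assignments that could not have occurred. The type I error figures are illustrative: they depend on the assumed trends and noise and, above all, on which of the two procedures is meant.

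The plan's 80% power statement could not be checked against this, since its effect size and figure are not in the text available.

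**What to change.** In protocol 2.4 and, where repeated, in the Data Analysis Plan for Primary Study Aim:

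1. Delete the figure 38,416, the alpha < .0001 claim and the independent permutation of TPs.
2. Define the reference set as the six site-to-date assignments. Count the observed assignment and ties (greater than or equal). State the smallest attainable p, 0.167 one-sided and 0.333 two-sided, and report the exact p as supportive only.
3. State that the GLMM or GEE already named gives the primary estimate. Settle which of the two is used, include calendar time in the model (the paragraph lists no such term), and report the effect with a confidence interval.
4. Label that estimate as model-dependent, and say that sandwich variances are unreliable with three randomised units.

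The cost is wording and some analysis programming; no data collection changes. The sponsor gives up the claim of very small design-based p-values, and the primary conclusion then rests openly on a model.

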examination of the population-level effect in the statistical models to make inferences about the treatment effect.

Power analyses for Aims 1 and 2: Estimates of power to detect significant differences for each hypothesis was conducted. Power analyses were conducted using G\*Power (v3.1.0), two-tailed hypothesis testing, and  $\alpha=.05$ ; results are presented separately for site level data (Figure 3). For site level data, the smallest effect size for Aims 1 and 2 proportion achieving undetectable viral load; power analyses for this “rate limiting” effect size used unconditional exact test to simulate permutation testing method of estimating p-values as well as simulated cluster permutation (i.e., TPs in a city covary together). The autocorrelation and clustering effects were modeled as overall “intraclass correlation” (ICC), using a range of ICCs observed in our prior studies. Results indicate 80% power is achieved with a sample size of 24 TPs (Figure 4).

[figure not shown]

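### The 80% power claimed for 24 trust points is not a power calculation for the stepped-wedge design: it describes no period effect and no assignment of three sites to three start dates.

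*Combined protocol and SAP*

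**What the plan says.** The power paragraph in Section 2.4 (Power analyses for Aims 1 and 2) uses G*Power, "two-tailed hypothesis testing" and alpha .05. It sizes the study on "the smallest effect size for Aims 1 and 2 proportion achieving undetectable viral load", which it calls rate limiting. The calculation for this "effect size used unconditional exact test to simulate permutation testing method of estimating p-values", and also "simulated cluster permutation (i.e., TPs in a city covary together". Autocorrelation and clustering enter as one overall ICC, "using a range of ICCs observed in our prior studies". The conclusion is "Results indicate 80% power is achieved with a sample size of 24 TPs". The readable text gives no effect size, baseline proportion or ICC value, and the power figure is not shown.

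Section 2.2 says "The unit under experimental control will be a city". Karaganda and Temirtau count as one site, so three sites are randomised to start in months 22, 28 and 34, and all TPs in a city switch together. The same section says the analysis will control for time-specific effects.

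Section 2.4 (Analysis of Program data) tests a difference in means between pre-implementation and BRIDGE periods by permutation, doubles the one-sided proportion for a two-sided p, and counts 38,416 clustered permutations. The Data Analysis Plan for Primary Study Aim adds GLMM or GEE with correlation within TP and within city. It names no period term.

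**The concern.** In a stepped wedge, exposure rises with calendar time in every site. A pre/post comparison therefore mixes the intervention with any secular change, and the comparison protected by randomisation is the one left after period is removed. An ICC describes correlation; it does not stand in for a period effect. A power figure headed by 24 TPs, with neither periods nor three-site assignment described, answers a different question from the one the design poses.

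This is the only numerical power claim in the plan. If it is too favourable for the analysis that respects the design, a non-significant result could be given more weight than it deserves, and nobody can tell from the text which effect the trial was sized to detect.

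**Working it through.** **The plan's own figures.** The 80% cannot be reproduced, because effect size, baseline proportion and ICC are not in the readable text. The permutation count can: 14^4 = 38,416, that is, four cities each free to take any of 14 positions. With the three sites actually randomised, the same count would be 14^3 = 2,744, with smallest one-sided p 1/2,744 = 0.00036, which does not support the stated alpha below .0001.

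**Inputs from the documents.** Three sites; 8 TPs per site (Section 3.7); quarterly measures over 42 months, so 14 quarters (Section 2.4); data from month 13 (Appendix A); starts in months 22, 28 and 34 (Section 2.2). The sites therefore have 3, 5 and 7 pre-quarters and 11, 9 and 7 post-quarters.

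**Test that follows the randomisation.** Three sites over three dates give 3! = 6 arrangements. The smallest one-sided p is 1/6 = 0.167, which the plan's rule doubles to 0.33. Counting absolute differences instead gives 0.167. Neither can fall below .05, so power is 0% for any effect.

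**Information lost by adjusting for quarter.**
- Exposure sum of squares after removing site means: 3×11/14 + 5×9/14 + 7×7/14 = 2.357 + 3.214 + 3.500 = 9.07.
- Quarter means of exposure are 0 (3 quarters), 1/3 (2), 2/3 (2) and 1 (7); the grand mean is 27/42 = 0.643. The between-quarter sum of squares is 3 × (3×0.643² + 2×0.310² + 2×0.024² + 7×0.357²) = 6.98.
- Remaining after site and quarter: 9.07 − 6.98 = 2.095. The ratio 9.07/2.095 is 4.3.

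**Standard error of the adjusted effect.** With TP-by-quarter residual SD 1 and city-by-quarter SD s (assumed 0 to 0.3, a within-period ICC of 0 to 0.08), SE = sqrt((s² + 1/8)/2.095).

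**Two benchmark effects that could lie behind the 80%** (both are assumptions):
- A: independent-TP pre/post comparison. SE = sqrt(mean(1/n_pre + 1/n_post)/24) = sqrt(0.340/24) = 0.119; effect = 2.80 × 0.119 = 0.334.
- B: 24 versus 24 units. Effect = 2.80 × sqrt(2/24) = 0.81, taken in residual SD.

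Power is from the noncentral t distribution. The 25 df are 42 site-quarter means less 3 sites, 13 quarters and 1 treatment term; 2 df reflects three randomised units.

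| s | ICC | SE | A, 25 df | B, 25 df | B, 2 df |
|---|---|---|---|---|---|
| 0 | 0 | 0.244 | 26% | 89% | 44% |
| 0.1 | 0.01 | 0.254 | 24% | 87% | 42% |
| 0.2 | 0.04 | 0.281 | 21% | 79% | 37% |
| 0.3 | 0.08 | 0.320 | 17% | 68% | 30% |

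Under A, the effect would have to be 2.1 to 2.8 times larger for 80% power with 25 df.

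**The case against.** Four stronger readings are tempting, and the documents support none of them.

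*TPs were treated as independent.* The power paragraph says otherwise: TPs in a city covary in the simulated permutation, and an ICC was used. Section 2.4 also reports the more conservative of the TP-level and city-clustered p-values. What is missing is the period effect and the three-site assignment, not all clustering.

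*The plan's own test has no power.* The named test permutes status by time point within city over 38,416 arrangements, so its smallest two-sided p is about 2/38,416 = 0.00005, not 0.33. The 0% belongs to a test that re-randomises as the trial did. The plan's permutation set escapes that floor only because it does not correspond to the allocation.

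*Only quarters 4 to 7, where exposed and unexposed sites coexist, carry information.* Those quarters alone give a sum of squares of 0.667, against 2.095 from all 14. The other quarters help to estimate the site effects.

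*The 80% is several-fold too high.* This follows under benchmark A but not under B, where model-based power with 25 df runs from below to above 80%. The text does not say which comparison was sized.

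It is also fair to say that Section 5 separately argues that the client pool is adequate. That argument concerns numbers of clients, not the power of a three-site comparison. These objections limit the size of the claim. They do not supply a period term or a three-site calculation.

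**Conclusion.** The power statement is wrong as written for this design: what it describes is not a stepped-wedge calculation. Two results need no assumption about effect size. A test faithful to the randomisation cannot reject at .05 (smallest two-sided p 0.33), and quarter adjustment reduces the treatment information 4.3-fold relative to the same unadjusted within-site comparison.

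The power of a period-adjusted model is not known. It is 17-26% if the 80% came from an independent-TP pre/post comparison. If it was sized as 24 versus 24 units, it is 68-89% with 25 df and 30-44% with 2 df. These ranges rest on the assumed benchmark effects, the assumed city-by-quarter SD of 0 to 0.3, the choice of degrees of freedom, a roughly normal outcome and the quarterly layout of the program measures. No single shortfall should be quoted.

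**What to change.** 1. Replace the 80% statement in Section 2.4 with the power, or the effect detectable at 80% power, of an analysis with fixed period effects and three randomised sites. Use 3 sites × 8 TPs × 14 quarters, a city-by-period variance and small-sample degrees of freedom, over the ICC range already used. State the assumed effect size, baseline value and ICCs in the text.
2. Add the period term to the GLMM/GEE in the Data Analysis Plan for Primary Study Aim, so that the control of time effects promised in Section 2.2 is in the model.
3. State that re-randomisation over the six possible assignments cannot reach .05, that the 38,416 arrangements are not the randomisation set, and that conclusions will rest on the model estimate and its interval.

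The cost is one calculation or simulation and edits to a few paragraphs, with no added enrolment or data. The downside is a stated figure that is likely to be less favourable.
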